All continuous data will be checked for normality using a Shapiro-Wilk test and by visually checking for skewness and kurtosis. Markers of bone and calcium metabolism, reproductive function, and musculoskeletal health will be compared between contraceptive groups with a one-way between-group analysis of covariance (EUM [day 14] vs COCP [day 21] vs hormonal implant vs IUS vs hormonal injection groups) controlling for age, lean body mass (for bone measures only), physical activity, total 25(OH)D, and previous hormonal injection use. Categorical data from questionnaires will be analyzed using a chi-square test to test for differences between lifestyle, prior HC use, menstrual cycle history, and dietary choices between groups. Nonnormally distributed data will be tested using a Kruskal-Wallis test. Significant main effects of the group will be followed up with post hoc 2-tailed *t* tests with a Bonferroni correction (or Mann-Whitney *U* test for nonparametric data). Paired-sample 2-tailed *t* tests will be used to compare markers of bone and calcium metabolism, and reproductive and musculoskeletal function across the 2 time points in COCP users. Markers of bone and calcium metabolism, reproductive function, and muscle strength and tendon function will be compared between days in the menstrual cycle for the EUM group with a linear mixed effects model with the restricted maximum likelihood estimator to allow incorporation of incomplete data. Time will be the fixed effect (day 1 vs day 7 vs day 14 vs day 21), and a random intercept will be assigned to participants to account for the nonindependence of repeated measures. The significance of the fixed effects from each model will be determined with Sattherwaite degrees of freedom. The normality of the residuals for each model will be checked visually by plotting the residuals against the fitted values and from Q-Q plots. In the event of a significant main effect of time, pairwise comparisons with Holm-Bonferroni corrections and Kerward-Roger degrees of freedom will be used on the linear mixed effects model to identify differences between time points. A Bland-Altman plot will be used to assess the agreement between aBMD measured by ultrasound and DXA. Differences will be considered statistically significant at an α level of *P*<.05 with post hoc *P* values corrected for multiple comparisons.

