### Limitations

The cross-sectional study design prevents standardized and controlled administration (frequency and dose) of HCs in the COCP group, and the self-selection of hormonal contraception across groups may introduce selection bias. A randomized control trial design of HC interventions was not considered feasible for this research due to the length of time needed to elucidate meaningful effects, the impact on lifestyle and health care for participants, and the invasive procedures for the administration of LARCs. Functional movement—visually assessed from the location of the midpoint of the knee and ankle using video footage—may also be subject to observer bias; this bias will be minimized by using a single trained observer. Investigators will also be involved in the testing of all study participants and will not be blinded to HC groups.

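### Outcomes judged non-normal lose the planned covariate adjustment, because the between-group analysis switches from ANCOVA to tests that take no covariates

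*Protocol article*

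**What the plan says.** All of this is in the protocol article, Statistical Analyses, unless noted.

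- **Main method.** Outcomes "will be compared between contraceptive groups with a one-way between-group analysis of covariance", "controlling for age, lean body mass (for bone measures only), physical activity, total 25(OH)D, and previous hormonal injection use".
- **Check.** "All continuous data will be checked for normality using a Shapiro-Wilk test and by visually checking for skewness and kurtosis".
- **Fallback.** "Nonnormally distributed data will be tested using a Kruskal-Wallis test".
- **Follow-up.** "Significant main effects of the group will be followed up with post hoc 2-tailed" t tests with a Bonferroni correction, or Mann-Whitney U tests for nonparametric data.
- **Cycle analysis, for contrast.** In the eumenorrheic group, the mixed model has its residuals checked, and its pairwise comparisons are explicitly made on the fitted model.
- **Group formation.** The Limitations section says that "the self-selection of hormonal contraception across groups may introduce selection bias".

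**The concern.** The groups are not randomised, and the ANCOVA covariates are the plan's only statistical control for differences between women who chose different methods. The plan does not merely leave the non-normal case open. It prescribes tests that cannot carry those covariates, at both the omnibus and the pairwise step.

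Three things follow.

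- Whether an outcome is adjusted depends on the shape of its distribution, not on whether it is confounded. Two bone markers in the same table could answer different questions, one adjusted and one not.
- The check is described as made on the data. ANCOVA assumes normal residuals, so the stated check does not test the model's own assumption.
- A difference in age, activity, 25(OH)D or lean mass between groups could be read as a contraceptive effect on any outcome sent to the fallback. The Dissemination Policy section says the results are meant to inform servicewomen and guide prescribers.

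**Working it through.** **Step 1. What is lost, from the text alone.** The table sets the two routes side by side.

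| Route | Omnibus test | Covariates | Pairwise test | Covariates |
|---|---|---|---|---|
| Judged normal | ANCOVA | yes | t tests, Bonferroni | not stated |
| Judged non-normal | Kruskal-Wallis | none possible | Mann-Whitney U | none possible |

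The second row needs no simulation. Of the listed covariates, previous injection use matters least here. The Recruitment section excludes anyone outside the injection group with a history of injection use, so that covariate nearly coincides with group. The real loss is age, physical activity, 25(OH)D and, for bone measures, lean mass.

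**Step 2. Inputs for the size.** The plan states no figure on this point to reproduce; its sample-size calculation concerns change across the menstrual cycle.

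- From the article: 5 groups of 20, alpha 0.05, and Bonferroni over 10 pairs = 0.05/10 = 0.005.
- Assumed, because the documents do not give them: one group is shifted by *s* = 0 to 1.0 SD on one covariate; the covariate's within-group correlation with the log outcome is *r* = 0.3 or 0.5; the outcome is log-normal; there is no true group effect.

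**Step 3. Expected size by formula.** Without adjustment, the shifted group differs on the log scale by δ = *r* × *s* SD. For an unadjusted one-way F test the noncentrality is

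λ = 20 × [4(δ/5)² + (4δ/5)²] = 16δ², with 4 and 95 degrees of freedom.

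- *s* = 0.5, *r* = 0.3: δ = 0.15, λ = 0.36, rejection probability 6.8%.
- *s* = 1.0, *r* = 0.5: δ = 0.50, λ = 4.0, rejection probability 30.5%.

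Kruskal-Wallis should come out close to these or slightly below. It depends only on ranks, so the degree of log-normal skew does not change it.

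**Step 4. Simulation, 3,000 runs per setting.** False-positive rates:

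| *s* (SD) | *r* | Kruskal-Wallis, 0.05 | ANCOVA on log, 0.05 | Mann-Whitney, one pair, 0.005 | Adjusted contrast, one pair, 0.005 |
|---|---|---|---|---|---|
| 0 | 0.3 | 4.6% | 5.3% | 0.2% | 0.4% |
| 0 | 0.5 | 5.1% | 5.4% | 0.2% | 0.4% |
| 0.5 | 0.3 | 6.2% | 4.3% | 0.5% | 0.3% |
| 0.5 | 0.5 | 10.2% | 5.6% | 1.7% | 0.3% |
| 0.8 | 0.3 | 11.0% | 5.5% | 1.7% | 0.5% |
| 0.8 | 0.5 | 19.0% | 4.8% | 4.5% | 0.5% |
| 1.0 | 0.3 | 12.1% | 6.0% | 2.7% | 1.0% |
| 1.0 | 0.5 | 28.3% | 4.8% | 7.2% | 0.4% |

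The simulation error is about 0.8 percentage points at 28% (√(0.283 × 0.717/3000) = 0.008) and 0.4 points at 5%. A separate run gave 7% to 29% for Kruskal-Wallis over the same range of imbalance. The results agree with Step 3.

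**Step 5. The post hoc t tests.** The cycle comparisons are stated to come from the mixed model. The between-group sentence names only t tests and does not mention adjusted means. Read literally, an adjusted omnibus result can be followed by unadjusted pairwise estimates.

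**The case against.** **Eligibility already controls confounding.** Age is limited to 18-40 years and BMI to 18-30 kg/m², women with 25(OH)D below 30 nmol/L are excluded, and the Strengths section credits these criteria with control. This stands in part: what is lost is statistical adjustment, not all control. The permitted ranges still leave room for groups to differ, and physical activity has no stated numerical limit.

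**The inflation rests on assumed inputs.** This stands. With no imbalance there is none, and at 0.5 SD with correlation 0.3 it is about one percentage point. The upper end needs a full SD of imbalance and a correlation of 0.5.

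**The t tests may already be adjusted.** Bonferroni comparisons of ANCOVA-adjusted means are also t tests, and a fuller protocol may say so. This stands: that part is an ambiguity to settle, not an established error.

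**Stronger readings that the documents do not support.**

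- A reader might infer that the post hoc t tests would be falsely significant very often. The plan runs them only after a significant group effect and at the Bonferroni level. With a normal outcome, no true group effect, 1 SD imbalance and correlation 0.5, literal unadjusted t tests behind the ANCOVA gate flag the affected pair in about 1% of trials, and any of the ten pairs in about 3%. What remains is possible bias in the pairwise estimates once a true group effect opens the gate.
- A reader might infer that a real group difference would often push an outcome to the fallback. With normal data and one group 1 SD apart, a pooled Shapiro-Wilk test fails in about 6.5% of trials, against 5% with no difference. The article does not say whether the check is pooled, and it adds a visual assessment.
- A reader might infer that Bonferroni is wrong because the cycle analysis uses Holm-Bonferroni. Both are valid, and the choice is one of preference.

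**Conclusion.** The point holds for the fallback rule. As written, any between-group outcome judged non-normal is analysed without the listed covariates at both steps, and that follows from the tests themselves. The size depends on assumptions. For an imbalance of 0.5 to 1.0 SD in one group and a covariate correlation of 0.3 to 0.5, the Kruskal-Wallis false-positive rate is about 6% to 29%, against about 5% for the adjusted analysis on the log scale. Both are nominal without imbalance.

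For the post hoc t tests the conclusion is weaker: the wording does not tie them to the ANCOVA, so the pairwise estimates may be unadjusted, and the text should say which is meant. The plan should be changed before analysis, but the problem does not affect data collection.

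**What to change.** Revise the Statistical Analyses section as follows.

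- Fit the covariate-adjusted model for every continuous between-group outcome.
- Judge normality on that model's residuals, as the plan already does for the mixed model.
- For skewed outcomes, log-transform, or use a rank-based or ordinal regression model with the same covariates, in place of Kruskal-Wallis and Mann-Whitney.
- State that the Bonferroni-corrected pairwise comparisons are contrasts of adjusted means (or the matching model contrasts) from that same model.

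No new data are needed beyond the covariates already planned. The cost is revised wording, a little more analysis work, and reporting log-transformed outcomes as geometric-mean ratios, which need a sentence of explanation for readers used to differences in means.

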### Aims and Hypotheses

There is limited evidence for the overarching effects of estrogen on bone and calcium metabolism and musculoskeletal performance and even fewer studies investigating the impact from chronic use of HCs. Our primary aims are to (1) investigate the effect of menstrual cycle phase on bone and calcium metabolism, and musculoskeletal health and performance in EUM, non-HC users (EUM group); and (2) investigate the effects of HC use on bone and calcium metabolism, and musculoskeletal health and function. Our secondary aims are to (1) determine the validity of an ultrasound-based method of measuring hip and spine aBMD compared with “gold standard” DXA and (2) compare calcium and bone metabolism, reproductive hormones, and musculoskeletal function between the pill phase and non-pill phase of COCP use.

This study will test the following hypotheses in 2 study designs. Menstrual cycle phase (within-groups design): (1) calcium and bone metabolism is decreased during the ovulatory phase compared with other phases; and (2) muscle strength and tissue mechanical properties differ across the menstrual cycle. HC use (between-groups design): (1) calcium and bone metabolism is higher in the implant and injection groups compared with IUS (which exerts localized effects) and EUM (ovulatory phase) groups, and lower in the COCP group; (2) estradiol and progesterone are lower in HC users compared with the EUM group during the ovulatory phase; (3) bone macro- and microstructure, muscle strength, and tissue properties are different in HC users compared with the EUM group; and (4) calcium and bone metabolism, reproductive hormones, and musculoskeletal function are different between the pill phase and non-pill phase of COCP use.

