## Methods

### Recruitment

Biochemical markers of bone and calcium metabolism and measures of musculoskeletal health and performance will be obtained in physically active women who are EUM (n=20) or HC users taking or administered COCP (n=20), implants (n=20), IUS (n=20), or hormonal injections (n=20). Participants will be aged 18-40 years; have stable body mass (defined as no change in self-reported body mass ≥5% over the previous 3 months); have a BMI between 18 and 30 kg/m^2^; have a regular menstrual cycle of 24-35 days in length; have not been taking any HC in the last 12 months (EUM group); have used the COCP for at least 12 months (COCP group); have used the IUS continuously for at least 2 years (IUS group); have used the implant continuously for at least 12 months (implant group); or have used the hormonal injection continuously for at least 2 years (injection group). Participants will be excluded if they have diagnosed premature ovarian insufficiency; are pregnant; are less than 2 years post partum; have given birth to more than 2 children; demonstrate evidence of disordered eating (defined as ≥20 on the Eating Attitudes Test-26 items) or have a self-reported eating disorder; report menstrual disturbance (amenorrhea or oligomenorrhea: <9 menstrual cycles in previous 12 months); are a habitual smoker (defined as ≥10 cigarettes per day); are taking any medication known to affect bone or calcium metabolism (eg, treatment for thyroid disorders); have a self-declared history of heart, liver or kidney disease, diabetes or thyroid disorder; self-report a bone injury in the previous 12 months; or have a total 25-hydroxyvitamin D (25(OH)D)<30 nmol/L at prescreening. Finally, any participants not in the injection group who report a history of using the hormonal injection will also be excluded from participation. We will aim to recruit matched sample sizes; however, some HC options are less common, and the study may be unable to achieve the desired sample size. Researchers have stated an end point for data collection of August 2024, giving 2.5 years of recruitment. If any group is underpowered, the sample achieved will be presented to mitigate influences from different time periods. An overview of the study schedule is illustrated in Figure 1; proposed biochemical markers of reproductive health and bone health are listed in Table 1.

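### Between-group follow-up uses plain Bonferroni where Holm, already used for the cycle model, controls the same error and never has less power

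*Protocol article*

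**What the plan says.** All points are from the protocol article.

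- **Groups compared (Statistical Analyses).** One-way analysis of covariance on five groups: "EUM [day 14] vs COCP [day 21] vs hormonal implant vs IUS vs hormonal injection groups". The Recruitment section sets a target of 20 per group, for example "implants (n=20), IUS (n=20), or hormonal injections (n=20".
- **Between-group follow-up.** "Significant main effects of the group will be followed up with post hoc 2-tailed *t* tests with a Bonferroni correction", with Mann-Whitney tests for nonparametric data. The number of pairs is not given.
- **Cycle-model follow-up, same paragraph.** "pairwise comparisons with Holm-Bonferroni corrections and Kerward-Roger degrees of freedom will be used on the linear mixed effects model". Four time points give 4 × 3 / 2 = 6 pairs.
- **Significance level.** "Differences will be considered statistically significant at an α level of *P*<.05 with post hoc *P* values corrected for multiple comparisons".
- **Hypotheses (Aims and Hypotheses, between-groups design).** Hypothesis (2): "estradiol and progesterone are lower in HC users compared with the EUM group during the ovulatory phase". Hypothesis (3): "bone macro- and microstructure, muscle strength, and tissue properties are different in HC users compared with the EUM group". Hypothesis (1), on calcium and bone metabolism, also sets the implant and injection groups against the IUS group, so it includes contrasts between contraceptive types.
- **Discussion, Primary Findings.** States an aim of comparing outcomes across types of contraceptive.

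**The concern.** Two familywise corrections appear in one paragraph. The less powerful one is applied to the between-woman comparisons, where each woman does not serve as her own control, groups are small, and the Recruitment section accepts that some may fall short of 20. No reason is given for the difference.

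At stake is some avoidable loss of power for real group differences in hormones, bone structure, strength and tissue properties. The type I error rate is not in question, since both methods hold the familywise rate at 0.05 or below.

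A second question is how large the family is. Hypotheses (2) and (3) name only contraceptive users against EUM, which is four contrasts. Follow-up of a five-group test would naturally cover ten.

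**Working it through.** **1. The plan's own figure.** The plan gives no between-group power. Its 8 to 17 participants concern the time effect at seven time points. With f² = η²/(1 − η²), noncentrality λ = f²·n·m/(1 − ρ), m = 7, and ρ = 0.5 with sphericity (both assumed):
- η² = 0.06: f = 0.253; n = 17 gives power 0.82.
- η² = 0.14: f = 0.403; n = 8 gives power 0.86.

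The figure reproduces, but it does not bear on the between-group tests. The η² range is borrowed below as an assumption.

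**2. Why Holm is never worse.** For m tests, Bonferroni rejects when p ≤ 0.05/m. Holm orders the p values and rejects p(i) while p(i) ≤ 0.05/(m − i + 1), stopping at the first failure. With m = 10 the thresholds are 0.005, 0.0056, 0.00625 and so on up to 0.05. The first equals Bonferroni's and the rest are larger, so every Bonferroni rejection is also a Holm rejection. This holds for any m and for any valid p values, including those from Mann-Whitney tests.

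**3. Size of the gain.** Five groups give 5 × 4 / 2 = 10 pairs (Bonferroni threshold 0.05/10 = 0.005), of which 4 involve EUM.

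Converting η² to a difference δ in SD units:
- One group apart from the other four: f = δ·√(0.2 × 0.8) = 0.4δ, so δ = 0.63 at η² = 0.06 and 1.01 at 0.14.
- Two groups (EUM and IUS) apart from the other three: f = δ·√(0.4 × 0.6) = 0.49δ, so δ = 0.52 and 0.82.

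Simulation, at least 20,000 trials per row: 20 per group, normal errors, no covariates, omnibus F test at 0.05 first, then ordinary two-sample t tests. Entries are average power per truly different HC-versus-EUM pair; simulation error is about one point.

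| Configuration | η² | δ | Bonferroni, 10 pairs | Holm, 10 pairs | Holm, 4 pairs |
|---|---|---|---|---|---|
| All four HC groups differ equally from EUM | 0.06 | 0.63 | 17% | 18% | 31% |
| Same | 0.14 | 1.01 | 58% | 61% | 79% |
| IUS equals EUM, other three differ | 0.06 | 0.52 | 10% | 11% | 18% |
| Same | 0.14 | 0.82 | 37% | 41% | 55% |
| One HC group differs | 0.14 | 1.01 | 58% | 61% | 70% |

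Holm for Bonferroni on the same ten pairs gains 1 to 4 points. Narrowing to four contrasts as well gains 8 to 21 points over the first power column (18 − 10 = 8; 79 − 58 = 21).

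Check without the gate, from the noncentral t: δ = 1.01 at α = 0.005 with 20 per group gives 59%, in line with the 58% above.

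**4. Outside that range.** If contraceptive groups differ from EUM in opposite directions (−0.9, +0.9, 0, +0.9 SD), Holm on ten pairs gains 9 to 10 points per HC-versus-EUM pair (46% to 55%). The group means then have variance 0.4536, so η² = 0.4536/1.4536 = 0.31, more than twice the plan's upper value.

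**5. Which outcomes could use four contrasts.** Hypothesis (1) needs implant and injection each against IUS and EUM (4 pairs), plus 2 to 4 pairs for COCP depending on what it is lower than: 6 to 8 of the 10. A four-contrast family would drop part of that hypothesis, so it could apply only to the outcomes of (2) and (3).

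**The case against.** Bonferroni is a standard, valid choice, and using different corrections in two separate analyses is not a contradiction. Both points stand, and they are why this is not an error. They do not supply a reason to prefer Bonferroni here.

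The size of the comparison family may be fixed in a fuller document that is not shown, and the article does not rule out four comparisons. That also stands. The change to Holm does not depend on it.

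A reader might infer that power is wasted because six of ten pairs are asked for by nobody. The documents do not support this. The all-pairs family is inferred, not written. Hypothesis (1) needs contrasts between contraceptive types. The Discussion aims to compare types, faults earlier studies for pooling progestogen-only methods, and wants the results to inform contraceptive choice. Those pairs serve a stated purpose.

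A reader might also cite the chance of finding all four true differences at the larger effect: about 27% as written against 69% with Holm on four contrasts. That comparison changes the family, the correction, the error term and the omnibus gate together, in the configuration most favourable to the smaller family. If the IUS group resembles EUM, which its localized action makes plausible, and the gate and tests are left alone, the chance of finding all true differences goes from 14% to 35%. Most of the improvement comes from dropping comparisons that the protocol says it wants.

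**Conclusion.** The point holds as a free improvement. The between-group follow-up uses a correction that Holm dominates, and Holm is already in the plan.

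The gain is about 1 to 4 percentage points of per-pair power. It rests on ten pairs, 20 per group, normal errors, no covariates and η² of 0.06 to 0.14. The article gives no between-group effect size, so those values are an assumption. If fewer pairs are tested the amount changes, but Holm is still never worse.

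The four-contrast family for hypotheses (2) and (3) is a genuine trade-off for the investigators to weigh: roughly 8 to 21 points under the same assumptions, when HC groups differ from EUM in one direction, against confirmatory status for comparisons between contraceptive types. Nothing here invalidates the planned analysis or inflates its error rate.

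**What to change.** **Recommended.** In Statistical Analyses, replace Bonferroni with Holm-Bonferroni for the between-group post hoc comparisons, covering both the t tests and the Mann-Whitney follow-up, and state how many pairs the family contains. Cost: one sentence; no extra participants or visits, no change in familywise error, no loss of power.

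**Optional.** For the outcomes of hypotheses (2) and (3) only, define the confirmatory family as the four HC-versus-EUM contrasts at two-sided 0.05 with Holm (or Dunnett) adjustment, and label pairs between contraceptive types exploratory. Keep the wider family for hypothesis (1). The cost is weaker inference on differences between contraceptive types for those outcomes, so adopt this only if the investigators rank the comparison with EUM above the Discussion's aim of comparing types.
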